### Sample size

This clinical trial set has a non-inferiority threshold of 7 (%) and a variance of 11 (%) for the positive control group. We predict a 2% real difference between the tested drug and positive control in transferrin saturation. The unilateral significance level is 2.5%, with an assurance of 80%. In the case of a 1:1 sample size between the control group and the experimental group, a total of 154 samples will be collected (77 of which will be in the control group and the experimental group, respectively). Considering a 20% drop-out rate, the actual planned inclusion number will be 186 cases.

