### Intervention

#### Experimental group

Iron polysaccharide complex (150mg) will be taken orally, 2 capsules per day, for 24 weeks. Participants will be treated with biosimilar epoetin (no need to dilute) intravenously with a single dose of 10,000U once a week during the maintenance period. At the same time, biosimilar epoetin dosage will be adjusted according to the measured hemoglobin concentration, as follows [7].
Discontinue biosimilar epoetin if Hb ≥ 130 g/L. Hb levels will be checked once every 2 weeks. If the Hb level drops to 110–130 g/L, the original biosimilar epoetin dose will be reduced by 25% or extended to once in 10 days for continuation.If Hb < 110 g/L, TSAT, and SF are met, biosimilar epoetin will be administered as a single dose of 10,000U at least three times, every 2 weeks. Also, the Hb values of participants will be evaluated once every 2 weeks. The maximum dose of biosimilar epoetin will be 10,000U twice a week. If TSAT and SF fail to meet the standard, the iron deficiency will be corrected first, and the biosimilar epoetin treatment regimen will be adjusted once TSAT and SF are within the desired range.

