### Dose adjustment within the next 24 weeks

If TSAT < 20% occurs during the test, the dosage of the iron agent will be adjusted as follows.
Iron polysaccharide complex: The iron polysaccharide complex prescription will be adjusted from one capsule daily to two capsules twice dailyIron sucrose injection: the prescription of iron sucrose injection will be adjusted from “100 mg/time, intravenous drop, once every two weeks” to “100 mg/time, once a week.” If SF ≥ 500 μg/L and/or TSAT ≥ 50% after the above treatment, iron supplementation therapy will be stopped and SF and TSAT will be reevaluated twice a week. If SF < 200 μg/L and/or TSAT < 20%, or SF 200–500 mg/L and/or TSAT 20%–50% are found twice consecutively, iron supplementation therapy will be restarted. Iron supplementation therapy is iron sucrose injection 100 mg/time, intravenous drip, once a week

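### The stop/restart rule names no arm and restarts iron as iron sucrose, so the comparator may enter the oral arm before week-12 TSAT, and neither analysis set deals with it

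*Protocol article*

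**What the plan says.** The primary endpoint is TSAT at week 12 (Primary endpoint). The Discussion states a non-inferiority hypothesis for the oral product against iron sucrose, and Sample size sets the margin: "This clinical trial set has a non-inferiority threshold of 7" percentage points.

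The section Dose adjustment within the next 24 weeks does three things:

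- It escalates iron in both arms on low TSAT: "If TSAT < 20% occurs during the test, the dosage of the iron agent will be adjusted as follows". Each arm has its own item, and each escalates its own product.
- It stops iron when ferritin is at least 500 μg/L and/or TSAT is at least 50%, with re-evaluation twice a week, and restarts it on ferritin and TSAT readings. No arm is named.
- It defines what is restarted: "Iron supplementation therapy is iron sucrose injection 100 mg/time, intravenous drip, once a week". Again no arm is named. The regular control regimen is the same 100 mg every two weeks (Control group).

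Data set category makes ITT, with nobody excluded after randomisation, the main set. It defines the per-protocol set by compliance, the main entry criteria and absence of prohibited drugs. Iron sucrose given under the dose-adjustment rule is not named there as a reason for exclusion.

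**The concern.** In a superiority trial, giving the comparator to some of the experimental arm costs power. In a non-inferiority trial it shrinks a true deficit and makes the desired conclusion easier to reach. If the restart sentence covers the oral arm, part of that arm's week-12 TSAT may be produced by intravenous iron and credited to the capsule under ITT. The usual cross-check, the per-protocol set, would not clearly remove these participants, because someone treated as the protocol directs is neither non-compliant nor taking a prohibited drug. At stake is whether a positive result can be attributed to the oral product, which is how the Objective and the Discussion frame the claim.

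**Working it through.** **Step 1: the two readings of the rule.**

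| Reading | Consequence |
|---|---|
| Stop/restart text covers both arms | An oral-arm participant who is stopped restarts on weekly iron sucrose, which is the comparator at twice its regular frequency |
| Stop/restart text covers the control arm only | No crossover, but the section gives the oral arm no stop or restart rule |

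Support for the first reading: the wording is generic, and the cost endpoint under Secondary endpoints uses the same generic term for a comparison between groups. Support for the second: the text runs on from the iron sucrose item, and its weekly regimen equals that item's escalated regimen. The document does not settle the matter, and each reading leaves a defect.

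**Step 2: reproduce the plan's sample size.** Inputs from Sample size:

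- Margin: 7 points.
- Spread, as the section words it: "a variance of 11 (%) for the positive control group".
- True difference between the drugs: 2 points, with no direction given.
- Error and power: 2.5% one-sided and 80%.
- Evaluable number: 154 in two equal arms, so 77 per arm.

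n per arm = 2 × SD² × (1.960 + 0.842)² / (7 − 2)² = 2 × 121 × 7.85 / 25 ≈ 76. The noncentral-t version gives 77 (power 80.03%), as stated. This requires 11 to be the SD and the 2 points to be against the oral drug. Taking 11 as a variance gives 7 per arm. I use SD 11 below.

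**Step 3: effect of crossover on the error rate.** Let c be the share of the oral arm that takes on the control mean by week 12. The documents do not give c, so it is an assumption.

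- Apparent deficit = true deficit × (1 − c).
- SE = 11 × √(2/77) = 1.773.
- P(declare non-inferiority) = Φ((7 − apparent deficit)/SE − 1.960).

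With the true deficit at the margin (7 points):

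| c | Apparent deficit | (7 − apparent)/SE | One-sided error |
|---|---|---|---|
| 0 | 7.00 | 0 | 2.5% |
| 1% | 6.93 | 0.039 | 2.7% |
| 5% | 6.65 | 0.197 | 3.9% |
| 10% | 6.30 | 0.395 | 5.9% |

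With all 93 per arm analysed, the SE is 1.613 and the last two rows become 4.1% and 6.4%.

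**Step 4: what share is plausible?** Assume TSAT is normal with SD 11 and mean 28 to 36 (means assumed). Then 2% to 10% of single readings are at or above 50%, and 7% to 23% are below 20%. If a stop can only follow an earlier escalation, and readings are treated as independent, the product of the two probabilities is:

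- mean 28: 0.234 × 0.023 ≈ 0.5%
- mean 32: 0.138 × 0.051 ≈ 0.7%
- mean 36: 0.073 × 0.102 ≈ 0.7%

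Stops on ferritin would add an amount the documents do not allow one to calculate. The rows from 1% to 10% are therefore an illustration, with the lower end more likely.

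**The case against.** The strongest reply is that there is no crossover at all. In the available text, list items have lost their bullets, and the stop/restart sentences continue the iron sucrose item without the break seen between items elsewhere. The restart would then be the control arm's own drug. This reading is possible and may be the intended one. It removes the bias but leaves the oral arm without a stop rule, so the scope still has to be stated.

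Second, even on the literal reading the path is narrow. The stop applies after the treatment just described, most directly after escalation for low TSAT. Low TSAT, escalation, high ferritin or TSAT, a stop, qualifying readings and a restart must all fall before week 12, with scheduled visits at weeks 4, 8 and 12. This stands, and it is why the share is probably small. It does not make the share zero: entry allows ferritin just under 500 μg/L and TSAT just under 50%, and twice-weekly re-evaluation permits a quick restart.

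Third, the model lifts a random share of the arm to the control mean, whereas real switchers are selected for high values. This also stands. The effect per switcher could be smaller or even uncertain in direction, or larger because the restart is weekly. The figures show scale and are not a forecast.

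Fourth, the role of the per-protocol set in the decision is commonly left to the analysis plan. Agreed, and its absence from the article is not the point. The point is that the definition given does not catch protocol-directed iron sucrose.

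A reader might also infer three stronger things that the documents do not support:

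- That the error is grossly inflated. A rate of about 12% needs c = 20%, and nothing in the protocol suggests a share of that size.
- That the Experimental group section opens a second route to intravenous iron: "If TSAT and SF fail to meet the standard, the iron deficiency will be corrected first". That sentence governs epoetin timing. For TSAT below 20%, the dose-adjustment section largely answers it by escalating the assigned product, and sustained low values are an exit criterion under Withdrawal and drop-out.
- That adjusting dose on TSAT is itself the flaw. The trigger is the same in both arms. It may compress the difference, but the documents give no basis for sizing that.

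**Conclusion.** The point holds in a limited form. The stop/restart text is ambiguous as to arm, and either reading needs correction. If it covers the oral arm, the comparator can enter that arm before the primary endpoint, ITT would count the result for the capsule, and the per-protocol set as defined would not clearly remove it. The expected direction favours a finding of non-inferiority.

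The size is probably small: about 2.7% to 5.9% one-sided error against 2.5% nominal, for crossover shares of 1% to 10%. That range rests on SD 11, 77 per arm, a true deficit at the margin, switchers taking on the control mean, and a share that is assumed. The issue is worth settling in wording before analysis. It does not show that the design fails.

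**What to change.** 1. Reconcile the dose-adjustment section so that it says which arm or arms the stop and restart text covers. This is the trial team's clinical decision, and no rule is proposed here.
2. Keep ITT as the main set. Define any iron sucrose given to an oral-arm participant after randomisation and before the week-12 TSAT as a reason for exclusion from the per-protocol set. Claim non-inferiority only if the lower limit of the two-sided 95% interval (oral minus intravenous) exceeds −7 in both sets.
3. Add a sensitivity analysis that uses the last TSAT before the switch, noting that this value may have been taken while iron was stopped. Report iron sucrose use and dose escalations by arm.
4. If only ITT succeeds, word the conclusion as concerning a TSAT-guided strategy that includes intravenous iron.

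The cost is wording in the protocol and analysis plan. The cost endpoint already requires iron use to be recorded, and what matters here is that the dates are kept. Requiring both sets slightly lowers the chance of success. The per-protocol set also conditions on events after randomisation, so it supports ITT and does not replace it.

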### Endpoints

#### Primary endpoint

TSAT will be measured at 12 weeks after baseline treatment.

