**Methods:**

This randomized controlled trial uses an open-label, parallel group design, where the efficacy and safety of maintenance hemodialysis (MHD) participants is evaluated. The experimental group is assigned erythropoietins and iron polysaccharide complex (two capsules each time, bid), and the control group is assigned erythropoietin and sucrose iron (100mg, 2w) injection. Participants (aged 18–75 years) undergoing maintenance hemodialysis were considered for screening. Inclusion criteria included hemoglobin (Hb) ≥110g/L and < 130g/L, transferrin saturation (TSAT) > 20% and < 50%, and serum ferritin (SF) > 200μg/L and < 500μg/L. Exclusion criteria included acute or chronic bleeding, serum albumin < 35g/L, hypersensitive C-reactive protein (HsCRP) > 10 mg/L, and severe secondary hyperparathyroidism (iPTH ≥ 800 pg/mL). Full inclusion and exclusion criteria are described in the “Methods” section. The primary endpoint is TSAT of the participants at week 12. Secondary endpoints include Hb, SF, hematocrit (Hct), HsCRP, pharmacoeconomic evaluation, drug costs, quality of life, and indicators of oxidative stress. The treatment will last for 24 weeks with a follow-up visit at baseline (within 7 days prior to initial treatment) and weeks 4, 8, 12, 16, 20, and 24 after initial treatment. This clinical research includes 9 hemodialysis centers in mainland China and plans to enroll 186 participants.

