### Setting and recruitment

A total of 186 subjects will participate in the study and will be recruited from 9 participating research centers (the hospital). Prior to recruitment, the investigator will carefully study the past condition, including but not limited to disease diagnosis and previous dialysis status of each participant. Researchers will fully consider the compliance of the participants within 24 weeks based on asking the participants. Informed consent forms (ICFs) will be obtained before collecting any participant data and participant information. After the participants sign the ICFs, the investigators will also sign the ICFs and record the informed consent process in the medical records. Hemodialysis participants eligible for inclusion in the trial will receive intravenous infusion (100mg total) of iron sucrose for 2 weeks after initial screening. If they still meet the inclusion criteria, they will be formally enrolled and started on medication. The treatment follow-up period of each participant is 24 weeks; the follow-up point of the screening and treatment period are shown in Fig. 2.

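### Non-inferiority is decided only on week-12 TSAT of a 24-week regimen; if the arms are still diverging then, it can be declared although the week-24 deficit reaches the margin

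*Protocol article*

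**What the plan says.** The abstract and the Primary endpoint section agree on one primary time point: "The primary endpoint is TSAT of the participants at week 12" and "TSAT will be measured at 12 weeks after baseline treatment". The abstract also gives the length of the regimen: "The treatment will last for 24 weeks with a follow-up visit at baseline", then visits every four weeks to week 24.

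Entry requires TSAT above 20% and below 50%, ferritin above 200 and below 500 μg/L, and at least 12 weeks of prior epoetin and iron (Inclusion criteria). The route and dose of that iron are not given. A run-in common to all follows: "Hemodialysis participants eligible for inclusion in the trial will receive intravenous infusion (100mg total) of iron sucrose for 2 weeks after initial screening" (Setting and recruitment). The criteria are then checked again.

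The Sample size section has one calculation, with a "non-inferiority threshold of 7 (%) and a variance of 11 (%) for the positive control group". It adds: "We predict a 2% real difference between the tested drug and positive control in transferrin saturation". No time point is attached to that difference. Week-24 TSAT appears under Secondary endpoints as a comparison of changes between groups. No margin is attached to it, and the default in Statistical analysis technique is a two-sided t-test.

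**The concern.** Both arms start from the same treated, iron-replete state. If oral iron delivers less than intravenous iron, the gap in TSAT has to open after randomization as the inherited iron is used. Similar TSAT at week 12 can therefore mean that oral iron maintains iron status, or that earlier iron has not yet run down. The primary comparison cannot separate the two.

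Carry-over makes the early difference smaller, and in a non-inferiority trial a smaller difference favors success. The stated objective is to compare two maintenance regimens in patients with corrected anemia, and the Discussion hopes to inform guidelines. A reader would naturally extend a positive result to the whole 24 weeks. The secondary week-24 comparison would not settle that, because a non-significant two-sided test does not show non-inferiority.

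**Working it through.** **Inputs from the Sample size section:** margin 7 points, spread 11, true difference 2 points against the oral product, one-sided alpha 2.5%, power 80%, 77 per arm.

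**Step 1. Reproduce the plan's figure.** With 11 as the SD:

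n per arm = 2 × 11² × (1.960 + 0.842)² / (7 − 2)² = 242 × 7.849 / 25 = 75.98, so 76 by the normal formula. The t-based calculation gives 77 per arm (power 80.0%), which matches the plan.

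Taken literally as a variance, 11 gives 2 × 11 × 7.849 / 25 = 6.9, or 7 per arm. Only the SD reading reproduces 77, and it is used below.

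**Step 2. Chance of declaring non-inferiority for a true deficit d.** The standard error is 11 × √(2/77) = 1.773. The test statistic is noncentral t with 152 degrees of freedom and noncentrality (7 − d)/1.773; the critical value is 1.976. At d = 2 the trial passes with probability 80%, at d = 7 with 2.5%.

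**Step 3. Week-12 result when the week-24 deficit is exactly 7.** The documents contain nothing on how fast TSAT falls when intravenous iron stops, so the time course is an assumption. If carried-over iron is lost by first-order decay with half-life h weeks, the deficit grows as 1 − 2^(−t/h). The share present at week 12 is then

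(1 − 2^(−12/h)) / (1 − 2^(−24/h)) = 1 / (1 + 2^(−12/h)).

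| Assumed time course | Share at week 12 | Week-12 deficit | Noncentrality | Passes at week 12 |
|---|---|---|---|---|
| half-life 2 weeks | 0.985 | 6.89 | 0.06 | 3% |
| half-life 4 weeks | 0.889 | 6.22 | 0.44 | 6% |
| half-life 8 weeks | 0.739 | 5.17 | 1.03 | 17% |
| half-life 12 weeks | 0.667 | 4.67 | 1.32 | 26% |
| half-life 24 weeks | 0.586 | 4.10 | 1.64 | 37% |
| linear divergence | 0.500 | 3.50 | 1.97 | 50% |

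A week-24 test with the same margin, SD and sample size would pass 2.5% of the time. Linear divergence is the limit of the first-order model as the half-life grows without bound.

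**Step 4. What a sequential week-24 test costs.** Assume a true difference of 2 points, SD 11 and 77 evaluable per arm at both visits. Each test statistic has mean 5/1.773 = 2.82 against a critical value of 1.96. The bivariate normal probability that both pass is 67%, 69% or 72% for correlations of 0.3, 0.5 or 0.7. Week 12 alone keeps its 80%.

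**The case against.** Iron-replete entry from a common treated state is the right starting point for a maintenance question, and a washout would study another population. Choosing 12 weeks over 24 is a legitimate design decision. No passage claims non-inferiority sustained to week 24. TSAT at week 24 is collected, as are Hb, ferritin and hematocrit at 0, 12 and 24 weeks, so fading would be visible. Ordering of secondary tests is often left to an analysis plan, and that plan is not shown. All of this stands, and it is why the point is not an error in the plan. What remains is that, as the article fixes it, visible fading would not change the non-inferiority conclusion.

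Three stronger readings are tempting, and the documents do not support them.

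- **A 50% chance of a misleading pass.** That figure needs linear divergence. Every first-order half-life in the table gives less, and at 2 weeks the excess over 2.5% is negligible.
- **Participants are loaded with intravenous iron.** The run-in totals 100 mg, which equals one scheduled control-arm dose (Control group section). Most carry-over would have to come from prior iron, whose route and dose are unstated.
- **Week 24 is an unbiased benchmark.** The section Dose adjustment within the next 24 weeks changes iron dosing when TSAT is low. It also writes the restart after a stop as iron sucrose, without limiting it to the control arm. The Exit criteria remove participants with low ferritin or TSAT within two consecutive months. These rules have longer to act by week 24. They can pull the arms together or remove poor responders, which would also favor non-inferiority.

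**Conclusion.** The point holds as an inexpensive improvement. The single non-inferiority decision cannot distinguish a maintained effect from iron that has not yet run down. For an oral product exactly at the margin at week 24, the chance of passing at week 12 runs from about 3% to 37% for half-lives of 2 to 24 weeks, and reaches 50% only under linear divergence, against 2.5% at week 24.

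These figures rest on 11 being the SD, on 77 evaluable per arm, and on time courses that are assumed. The direction follows from the design if the arms are still diverging at week 12; the size cannot be derived from the documents. The 2.5% comparison further assumes that dose changes, restarts and exits do not distort week 24.

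**What to change.** Keep week-12 TSAT as the primary endpoint. Name week-24 TSAT as the first key secondary in a fixed sequence: if week 12 meets the 7-point margin, test week 24 for non-inferiority with the same margin at one-sided 2.5%. Claim non-inferiority over the 24-week regimen only if both are met. If only week 12 is met, limit the conclusion to 12 weeks, and do not describe the population as loaded with intravenous iron.

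State how the week-24 analysis treats iron dose changes, restart with iron sucrose, and exits for low ferritin or TSAT. The restart text must be reconciled with the arm-specific treatment sections, so that it is clear to which arm it applies.

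The test uses data already planned, with no extra visits or patients, no additional alpha, and no loss of power for the primary. The work lies in settling and writing down the handling of those events. The downside is a harder 24-week claim: about 67% to 72% chance of success under the assumptions of step 4, against 80% for week 12 alone.

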#### Secondary endpoints

TSAT of participants’ changes between groups at 24 weeks of treatmentHb, SF, Hct, and HsCRP values of participants’ changes between groups at 0, 12, and 24 weeks of treatmentDrug costs for participants’ changes between groups at 24 weeks of treatment (including cumulative biosimilar epoetin dose and iron supplementation)Quality of life scale scores EQ5D-5L of participants’ changes between groups prior to treatment and at 24 weeks of treatment [12]Indicators of oxidative stress, including malondialdehyde (MDA), superoxide dismutase (SOD), and glutathione peroxidase (GSH-Px), will be measured in participants’ changes between groups at 0, 12, and 24 weeks of treatment [12]Cardiovascular events during the follow-up

### Withdrawal and drop-out

Participants can withdraw from the clinical trial at any time for any reason without prejudice to the investigator’s right to treat their disease. After fully considering the benefit of the participants, the investigator has the right to request the participants to withdraw for any reason, such as the occurrence of concomitant disease, adverse events [13], or treatment failure. The ethics committee reserves the right to request withdrawal of the participants for program violation, administrative reasons, or other valid and ethical reasons. All participants withdrawing from the clinical trial must complete a final trial evaluation. And the reason for withdrawal will be stated in the eCRF with all other appropriate and valuable information. Specific discontinuation and exit criteria are listed below.

Discontinuation criteria:
Participants not having used the drug even onceWithout any test records or follow-up data, no safety and efficacy data recordsAffecting the trial evaluation by using prohibited treatments and drugs in the protocol within the next 24 weeksOther serious breaches of the scheme (participants with serious non-compliance to discharge criteria)

Exit criteria:
Exit requested by the participantsRecurring intolerable adverse reactionsSF ≤ 200 μg/L or TSAT ≤ 20% within 2 consecutive monthsHb concentration < 90 g/L or > 130g/L within 2 consecutive monthsPoor compliance, failure to comply to protocol thus affecting efficacyStudy observations could not be continued due to unforeseen circumstances occurring during the test

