### Trial design

This study is a multicenter, parallel controlled, randomized, open clinical trial (version 1.1; date 11 Dec. 2019, phase IV post-marketing) in China, which has been registered with the Chinese Clinical Trial Registry (http://www.chictr.org.cn/index.aspx) on March 23, 2020. The trial registration number is ChiCTR2000031166. The detailed flowchart is shown in Fig. 1. All eligible participants will be randomly divided into two groups in a 1:1 ratio: experimental group [conventional drug (erythropoietin) therapy+ iron polysaccharide complex] and control group [conventional drug (erythropoietin) therapy + iron sucrose injection]. Participants will complete the study visit at baseline (within 7 days before the first treatment) and weeks 4, 8, 12, 16, 20, and 24 after the first treatment. We used the SPIRIT reporting guidelines [11] in the current study.

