#### Data set category

Intention-to-treat (ITT): No one was excluded from the main analysis set after randomizationPer-protocol set (PPS): Good compliance case data that meets the main inclusion and exclusion criteria without affecting the main curative effects of prohibiting drugs within the next 24 weeksSafety set (SS): Case data involving usage of the investigational drug product at least once, including safety evaluation

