#### Statistical analysis technique

The number of participants selected and completing follow-up visits in the population and centers will be listed separately, and the three analysis data sets (ITT, PPS, SS) as specified above will be identified [14]. Cases of protocol violation should also be listed and the reasons indicated. In terms of outcome indicator analysis, continuous variable indicators will count the number of cases (*n*), mean ($$ \overline{x} $$), standard deviation (*SMD*), median (*M*), minimum (*min*), and maximum (*max*). The difference between groups will be analyzed using Student’s *t*-test. Counting and grading data will be used to calculate the frequency and composition ratio. The *χ*^2^ test/chi-square test will be used for differences between groups. Unless otherwise stated, all statistical tests will be conducted in a bilateral manner. For example, if *P* ≤ 0.05, the difference between groups is statistically significant. Results of this clinical trial will be analyzed using SAS version 9.2 or above software.

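### An exit rule based partly on TSAT can end participation before the week-12 TSAT is taken; if exits then drop out of the comparison and oral iron is worse, the result leans toward non-inferiority

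*Protocol article*

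**What the plan says.** All references are to the protocol article.

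- Primary endpoint: "TSAT will be measured at 12 weeks after baseline treatment".
- Trial design places visits at baseline and at "weeks 4, 8, 12, 16, 20, and 24 after the first treatment".
- Withdrawal and drop-out lists, among the exit criteria, serum ferritin at or below 200 μg/L "or TSAT ≤ 20% within 2 consecutive" months. The rule is the same in both arms, and its TSAT cut-off equals the lower entry limit for TSAT.
- The same section adds: "All participants withdrawing from the clinical trial must complete a final trial evaluation". It does not mention a week-12 TSAT after exit.
- Data set category defines ITT thus: "No one was excluded from the main analysis set after" randomization.
- Statistical analysis technique names Student's t-test for continuous outcomes, without saying which value represents week 12 for someone who has left.
- Dose adjustment handles low TSAT inside the trial: "If TSAT < 20% occurs during the test, the dosage of the iron agent will be adjusted as follows".
- Sample size: "This clinical trial set has a non-inferiority threshold of 7 (%) and a variance of 11 (%) for the positive control group".

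**The concern.** One limb of the exit rule is defined on the variable that forms the primary endpoint. A participant with TSAT at or below 20% at weeks 4 and 8 could be out of the trial before week 12. The article then offers an exit evaluation, not a week-12 value, so an analysis that keeps everyone randomized cannot be carried out with observed week-12 data alone.

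The missingness follows from a poor outcome, so it will be more common in whichever arm holds TSAT less well. If that is the oral arm, and the comparison uses only the week-12 values that exist, low values are lost mainly from that arm and the two means move together. In a non-inferiority trial that error favours the claim being tested. An analysis plan can model or impute the lost values, but it cannot recover them.

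**Working it through.** **1. The plan's own figure.** Inputs from Sample size: margin 7, spread 11, assumed difference 2, one-sided 2.5%, power 80%.

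n per arm = 2 × SD² × (1.960 + 0.842)² / (margin − deficit)² = 2 × 121 × 7.85 / 5² = 76. Adding the usual t correction, 1.96²/4 = 0.96, gives 77 per arm, or 154 in total, as stated.

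Other readings do not reproduce it: 11 as a true variance gives 7 per arm, a difference of 0 gives 39, and a difference of 2 in favour of oral iron gives 24. The plan therefore uses SD 11 and assumes oral iron to be 2 points worse. On that assumption exits for low TSAT would be more frequent in the oral arm.

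**2. Timing.** Weeks 4 and 8 are the two scheduled visits after the start of treatment and before week 12. If two consecutive months means two consecutive monthly visits, the rule can act at week 8.

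**3. Model.** From the document: SD 11, margin 7, and 93 randomized per arm (186/2). Assumed: normal TSAT at weeks 4, 8 and 12, constant arm means, equal correlation between visits, exit if TSAT ≤ 20% at both weeks 4 and 8, and no other drop-out. Control mean and correlation are not in the document and are varied. The ferritin and Hb limbs and the iron-dose change are not modelled.

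For apparent deficit D, P(non-inferiority) = Φ((7 − D)/SE − 1.96), with SE = √(s²/n control + s²/n oral) and n = 93 × (1 − exit proportion) when exits are dropped.

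Check with everyone measured: SE = 11 × √(2/93) = 1.61. A true deficit of 7 gives Φ(−1.96) = 2.5%. A true deficit of 2 gives Φ(5/1.61 − 1.96) = 0.87.

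**4. True deficit exactly 7 points.**

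| Control mean, correlation | Exits, control / oral | Exits dropped: apparent deficit | False non-inferiority | Exit-visit value used: apparent deficit | False non-inferiority |
|---|---|---|---|---|---|
| 30, 0.5 | 7.6% / 23.2% | 5.53 | 14.1% | 7.48 | 1.2% |
| 30, 0.8 | 11.5% / 29.4% | 4.55 | 35.6% | 7.17 | 2.0% |
| 33, 0.5 | 4.1% / 15.0% | 5.86 | 10.4% | 7.41 | 1.4% |
| 33, 0.8 | 6.9% / 20.6% | 5.07 | 24.1% | 7.21 | 1.9% |
| 36, 0.5 | 2.1% / 9.1% | 6.22 | 7.0% | 7.35 | 1.5% |
| 36, 0.8 | 3.9% / 13.4% | 5.53 | 15.9% | 7.15 | 2.0% |

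In the second row, 93 × 0.885 = 82 control and 93 × 0.706 = 66 oral participants remain. With control means of 28–35% and correlations of 0.5–0.8, the apparent deficit is 4.2–6.1 points and false non-inferiority is about 7–43%.

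**5. Other true effects (grid of step 4, exits dropped).** With a true deficit of 2, exits are 2–12% against 3–16%, the apparent deficit is 1.4–1.8, and P(non-inferiority) is 0.90–0.96 instead of 0.87. With equal arms, exits are equal and there is no bias.

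**6. Closer to the document's own rules (control mean 28–35%, exits dropped, true deficit 7 at week 12).**

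- Entry TSAT limited to 20–50%: false non-inferiority about 6–27%.
- The deficit also builds linearly to 7 points at week 12 (an assumption): exits 4–12% oral against 2–6% control, apparent deficit 6.3–6.8, false non-inferiority about 3–8%.
- Exit-visit value used instead of dropping exits: about 1–2.6% under a constant deficit and about 2–4% under a gradual one.

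**The case against.** The strongest reply is that the article never says exits are dropped. ITT excludes no one, everyone who withdraws has a final evaluation, and the t-test is not restricted to observed week-12 values. Missing-data handling belongs to an analysis plan that is not shown. This stands as far as it goes: the bias is conditional, and its direction can reverse if the exit-visit value is used. The drop-out allowance in Sample size fits leavers being lost to the analysis, but it sets no analysis rule. What the reply does not remove is a stated rule that can end participation on the endpoint variable before the endpoint is taken.

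The timing is also a reading. Two months of low values counted from week 4 end at week 12, and then few or no exits would precede the endpoint. The assessment schedule is in a figure that is not available, so TSAT testing at weeks 4 and 8 is inferred, although the dose-adjustment rule implies some interim testing.

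The largest figures ignore the entry limits and any gradual onset of the deficit. None includes the iron-dose change for low TSAT, which would reduce the effect further. That objection stands, and the lower ranges answer part of it.

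Three stronger inferences are tempting but not supported:

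- That the worst values are simply removed. Only participants low at both early visits leave before week 12; those first low at week 8 or 12 stay.
- That the ITT definition is contradicted. It is only that the definition cannot be met with observed week-12 values alone.
- That the ferritin and Hb limbs act in the same way. They touch TSAT only through correlation, and Hb above 130 g/L does not select low TSAT.

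**Conclusion.** The point holds in conditional form. The exit rule depends in part on the primary-endpoint variable and, if read as low at weeks 4 and 8, can act before the endpoint. Bias toward non-inferiority then needs two further conditions: oral iron holding TSAT less well, which the sample size implies, and exits dropping out of the comparison, which the article neither states nor excludes.

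Under both conditions and a true deficit equal to the margin, false non-inferiority ranges from about 3–8% (entry limits and gradual deficit) to 7–43% (neither modelled), against a nominal 2.5%. Use of the exit-visit value keeps it near nominal. These sizes rest on assumed control means and correlations. A reader might infer that the comparison is certain to be biased; the document does not establish that.

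Severity: should be fixed. Confidence: moderate.

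**What to change.** 1. Leave the clinical thresholds to the clinicians. Reconcile the exit criterion for low TSAT with the dose-adjustment rule for low TSAT, and say what two consecutive months means in terms of visits.
2. Separate leaving study treatment from ending data collection.
3. Take week-12 and week-24 TSAT from every randomized participant, whatever the exit status or the iron then received.
4. Analyse all randomized participants. For any week-12 value still missing, use a model-based method that draws on the week 4 and 8 values (a mixed model for repeated measures or multiple imputation), with a sensitivity analysis that shifts the missing oral-arm values down by the 7-point margin.
5. Report exits by arm and reason.

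The cost is protocol wording, one blood result per exited participant at each of these time points, and a little more analysis. Participants attend dialysis three times a week, so the sample can be taken at a routine session.
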